## 2. Materials and Methods

### 2.1. Participants

A total of 54 professional male and female athletes aged 18–25 years will be recruited from collaborating sports clubs located in the Attica region of Greece. Eligible participants will be athletes participating in open-skill sports, including football, basketball, volleyball, and handball, who have sustained at least one chronic lower-limb musculoskeletal injury lasting more than three months. Recruitment will be conducted in collaboration with team coaches and sports medicine professionals affiliated with these clubs. Participants will be randomly assigned in a 1:1:1 ratio to one of three groups: the experimental group, the placebo group, or the control group (*n* = 18 per group). Randomization will be performed using a computer-generated random allocation sequence by an independent researcher who is not involved in participant recruitment, outcome assessment, or statistical analysis. Allocation concealment will be ensured using sequentially numbered, opaque, sealed envelopes. Participants, outcome assessors, and statisticians will remain blinded to group allocation throughout the study.

Sample size was calculated using G*Power software (version 3.1.9.7; Heinrich Heine University Düsseldorf, Düsseldorf, Germany) [47]. The calculation was based on a mixed-design repeated-measures ANOVA with three groups (experimental, placebo, and control) and three measurement time points (baseline, post-intervention, and four-week follow-up). Assuming a medium effect size (f = 0.25), an alpha level of 0.05, statistical power of 0.95 and equal allocation across groups, the minimum required sample size was estimated at 48 participants. To account for an anticipated dropout rate of approximately 10%, the final target sample size was set at 54 participants, with 18 participants allocated to each group. A medium effect size of Cohen’s f = 0.25 was selected as a realistic estimate for a non-invasive psychophysiological intervention (BB) targeting psychological and Performance outcomes. This estimate was considered appropriate because previous intervention studies examining kinesiophobia and rehabilitation-related outcomes in athletes with lower-limb injuries have reported comparable sample sizes (33–51 athletes) and medium effect estimates (0.25–0.40) [48,49,50].

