### 2.5. Statistical Analysis

Data will be summarized using descriptive statistical methods. Continuous variables will be presented as means and standard deviations, whereas categorical variables will be expressed as frequencies and percentages. Normality of continuous variables will be assessed using the Shapiro–Wilk test.

Baseline demographic, anthropometric, and clinical characteristics will be compared across the three study groups to assess baseline comparability. Continuous variables will be analyzed using one-way analysis of variance (ANOVA) or the Kruskal–Wallis test, as appropriate, whereas categorical variables will be compared using Pearson’s chi-square test or Fisher’s exact test. Ordinal variables will be analyzed using the chi-square test for trend where applicable. If clinically meaningful baseline imbalances are detected, adjusted analyses using mixed-design ANCOVA models will be conducted.

The primary analysis will follow the intention-to-treat principle, whereby all randomized participants will be analyzed in the groups to which they were originally allocated, regardless of adherence to the intervention protocol or study completion. Missing data will be examined before analysis by assessing the extent and pattern of missingness. Where appropriate, missing values will be handled using multiple imputation procedures, and sensitivity analyses will be performed to evaluate the robustness of the findings.

To investigate changes across the 4-week BB intervention period (Time factor) and differences among the three groups (experimental, placebo, and control), a mixed-design analysis of variance (ANOVA) will be performed. The assumptions of the mixed-design repeated-measures ANOVA, including normality of the model residuals, homogeneity of variances, and sphericity, will be assessed before analysis. This analysis will assess the main effects of Time (within-subjects factor) and Group (between-subjects factor), as well as their interaction [78]. When significant effects are identified, post hoc pairwise comparisons will be performed with appropriate adjustment for multiple comparisons. If clinically meaningful baseline imbalances are detected, adjusted analyses using mixed-design ANCOVA models will be conducted.

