The clinical relevance of the findings was determined using partial eta squared (η^2^) as an index of effect size. Effect sizes were interpreted as small (η^2^ ≥ 0.01), moderate (η^2^ ≥ 0.06), or large (η^2^ ≥ 0.14) [67]. For continuous outcomes, estimated mean differences, standardized effect sizes, exact *p*-values, and corresponding 95% confidence intervals (95% CI) will be reported as appropriate. For categorical outcomes, odds ratios with 95% CI will be reported where applicable. All statistical analyses will be performed using SPSS version 29.0, with statistical significance set at *p* < 0.05.

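### Clinical relevance is tied to partial eta squared cut-offs, which cannot measure it: with no Group × Time effect the index is at least 'small' in 90% of trials and at least 'moderate' in 17% (N = 54)

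*Protocol article*

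**What the plan says.** Section 2.5 (Statistical Analysis) sets a mixed-design ANOVA for the outcomes: "This analysis will assess the main effects of Time (within-subjects factor) and Group (between-subjects factor), as well as their interaction". It then gives the rule for interpretation: "The clinical relevance of the findings was determined using partial eta squared", described as an index of effect size, followed by "Effect sizes were interpreted as small (η^2^ ≥ 0.01), moderate (η^2^ ≥ 0.06), or large (η^2^ ≥ 0.14".

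The section does not confine these labels to effects that reach significance. It sets significance at p < 0.05 and provides adjusted post hoc comparisons after a significant effect. For continuous outcomes it also plans mean differences, standardised effects, exact p-values and 95% confidence intervals, where appropriate. It does not link clinical relevance to any of these.

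Section 2.1 (Participants) gives the design: "three groups (experimental, placebo, and control) and three measurement time points (baseline, post-intervention, and four-week follow-up". The planned size is 54 randomised athletes, 18 per arm, with a minimum of 48. The primary analysis in section 2.5 follows intention to treat in all randomised participants.

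**The concern.** The article states a rule for clinical relevance, and the statistic it names cannot serve that purpose. Partial eta squared is the effect sum of squares divided by effect plus error sums of squares. Three properties matter here.

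- **No direction.** Benefit and harm of the same size give the same value.
- **No location.** The interaction has four degrees of freedom. With equal arms, a shift in the control arm alone gives the same value as the same shift in the experimental arm alone. Under section 2.4 the placebo arm receives the same music and guidance without the beats, so experimental minus placebo is the contrast that isolates binaural beats. The index does not single it out.
- **Upward bias in small samples.** It cannot be negative, so its average under no effect is above zero. Here that average lies well above the 'small' cut-off.

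At stake is the stated clinical conclusion. A paper that follows this text could attach a relevance grade to an interaction that is noise, or to one that says nothing about the beats.

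**Working it through.** **1. The plan's own sample size.** The inputs from section 2.1 are: "Assuming a medium effect size (f = 0.25), an alpha level of 0.05, statistical power of 0.95 and equal allocation across groups", and "the minimum required sample size was estimated at 48 participants". The dropout step reproduces: 48 / 0.90 = 53.3, so 54 (18 per arm). The figure of 48 depends on a within-person correlation that the article does not give. For the interaction, with λ = f²·N·m/(1 − ρ), m = 3 visits and sphericity, ρ = 0.5 gives power 0.930 at N = 48; power 0.95 there needs ρ of about 0.54. This does not affect what follows, which uses only the design and N.

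**2. Degrees of freedom for Group × Time.** df1 = (3 − 1)(3 − 1) = 4 and df2 = (N − 3)(3 − 1), which is 102 at N = 54 and 90 at N = 48.

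**3. Distribution under no effect.** Partial eta squared = df1·F/(df1·F + df2). With no true effect, and normality and sphericity, it follows Beta(df1/2, df2/2). With df1 = 4 and b = df2/2, the upper tail has a closed form:

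P(η² ≥ c) = (1 − c)^b · (1 + b·c), with mean 4/(4 + df2).

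- N = 54, b = 51: mean 4/106 = 0.038.
  - c = 0.01: 0.99^51 × 1.51 = 0.5990 × 1.51 = 0.904
  - c = 0.06: 0.94^51 × 4.06 = 0.0426 × 4.06 = 0.173
  - c = 0.14: 0.004
- N = 48, b = 45: mean 4/94 = 0.043.
  - c = 0.01: 0.99^45 × 1.45 = 0.6362 × 1.45 = 0.922
  - c = 0.06: 0.94^45 × 3.70 = 0.0618 × 3.70 = 0.229
  - c = 0.14: 0.008

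A simulation of 20,000 null trials at each size agreed: 90.3% and 17.4% at N = 54, and 92.4% and 22.6% at N = 48.

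**4. The cut-offs as p-values.** The same tail is the p-value of an observed index. At N = 54, an index of 0.01 corresponds to p = 0.90 and 0.06 to p = 0.17.

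**5. If the labels apply only to significant interactions.** Setting the tail equal to 0.05 gives the smallest significant value.

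- N = 54: c = 0.088, since 0.912^51 × 5.488 ≈ 0.050.
- N = 48: c = 0.099, since 0.901^45 × 5.455 ≈ 0.050.

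Both exceed 0.06. Every significant interaction is then at least 'moderate', and the first two grades add nothing to p < 0.05.

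**6. Sensitivity.**

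| Effect, N = 54, no true effect | P(≥ 0.01) | P(≥ 0.06) |
|---|---|---|
| Group × Time, sphericity | 90% | 17% |
| Group × Time, both df scaled by ε = 0.75 (assumed) | 86% | 19% |
| Group | 77% | 21% |
| Time | 60% | 4% |

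With ε = 0.75 the critical value at N = 54 rises to about 0.097, so step 5 still holds.

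**The case against.** The best defence is that the text calls partial eta squared an index of effect size and attaches its grades to effect sizes: "Effect sizes were interpreted as small" and so on. No value is named as the point at which a result becomes clinically relevant, and 'small' could be read as not relevant. This stands in part: the article never says that 0.01 or 0.06 amounts to clinical relevance. But the preceding sentence says clinical relevance is determined by this index, and the grades are the only guide given for reading it.

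Second, a 'moderate' label at 0.06 would appear beside a non-significant p-value, with mean differences and confidence intervals. That also stands. A reader might infer a 17% to 23% rate of false claims of efficacy, and the article does not support that. Under the null, an interaction that is both significant and at least 'moderate' occurs in about 5% of trials, as the test intends. The larger figures are the rates at which the label alone is earned.

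Third, pairwise comparisons and mean differences would show direction and location. They would, but the relevance criterion does not use them.

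A reader might also set a 'moderate' index against measurement error on the TSK-17 and conclude that it lies within that error. The article does not support this. It gives no TSK-17 standard deviation for these athletes, and its reliability figure comes from people with chronic low back pain. An individual's detectable change is also not the yardstick for a difference between group means.

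Finally, the lack of a minimal important difference is not itself the point, because a full protocol or analysis plan may supply one. The point is the criterion that the article does fix.

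**Conclusion.** The rule is wrong as written and should be changed. It does not assess clinical relevance on either reading. Applied to all results, it grades a null interaction at least 'small' in 90% of trials and at least 'moderate' in 17% with 54 analysed (92% and 23% with 48). Applied to significant interactions only, it makes all of them at least 'moderate'.

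These figures are for Group × Time under no true interaction and sphericity, and should not be carried over to the main effects. N = 54 is the natural base because the primary analysis is by intention to treat; N = 48 is the lower case. The results need no assumed standard deviation or within-person correlation. The significance test, the estimates and the confidence intervals are unaffected. The damage is confined to the clinical interpretation.

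**What to change.** In section 2.5, delete the statement that partial eta squared determines clinical relevance. If the index is kept, call it descriptive and say which effect it refers to.

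In its place, state that clinical relevance will be judged from between-group mean differences with 95% confidence intervals in the units of each outcome, chiefly experimental minus placebo on TSK-17, against a threshold in TSK-17 points fixed and justified before unblinding.

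The estimates and intervals are already planned, so data collection, sample size and the primary test do not change. The cost is one or two sentences and the work of agreeing the threshold. Whether the difference should be adjusted for baseline is a separate matter, and this change does not depend on it.

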## 3. Discussion

Lower-limb musculoskeletal injuries (MSK-I) are highly prevalent among professional athletes participating in open-skill sports and are associated with impaired return to sport (RTS), recurrent injury, reduced athletic performance, and persistent psychological distress [14,15,16,17]. Among the psychological factors influencing RTS, kinesiophobia has been identified as an important determinant of reinjury anxiety, movement avoidance, reduced self-confidence, impaired concentration, and decreased athletic performance [17,18]. Fear of reinjury and pain-related anxiety may also affect autonomic nervous system (ANS) regulation by increasing psychophysiological arousal, sympathetic activation, and altered cardiovascular responses.

The present study is based on a biopsychophysiological framework linking kinesiophobia, ANS regulation, and auditory stimulation using binaural beats (BB). Changes in skin electrical activity and heart rate variability (HRV) following BB stimulation may help characterize physiological responses associated with kinesiophobia, fear of reinjury, and related physiological biomarkers. In this context, changes in skin electrical activity, assessed using the Sympathetic Skin Response (SSR), reflect sympathetic ANS activity, whereas HRV provides information regarding cardiac autonomic regulation. Therefore, the simultaneous assessment of psychological outcomes (e.g., kinesiophobia, fear avoidance, anxiety, and pain beliefs), HRV, handgrip strength, and fitness-related biomarkers (VO_2_max and blood lactate accumulation) may provide a multidimensional evaluation of the interaction between psychological and physiological factors in athletes participating in open-skill sports with chronic lower-limb MSK-I.

Contemporary sports rehabilitation increasingly supports the integration of complementary psychophysiological interventions alongside conventional physical rehabilitation protocols. Acoustic stimulation interventions, including binaural beats (BB), have attracted growing scientific interest because of their potential effects on anxiety regulation, pain perception, attentional control, autonomic modulation, and psychophysiological performance [37,38,39,40,41,42,43,45]. Previous studies suggest that BB stimulation may reduce anxiety, improve attention, modulate pain perception, and influence ANS function [40,41,43,45].

However, limited evidence exists regarding the effects of BB in professional athletes with chronic lower-limb MSK-I, particularly with respect to kinesiophobia, autonomic function, handgrip strength, HRV, and fitness-related biomarkers. The present study therefore aims to address this gap by investigating whether a music-based binaural beats intervention can influence psychological and physiological outcomes relevant to fear of reinjury. It is hypothesized that reductions in kinesiophobia, competitive anxiety, and maladaptive pain beliefs will be accompanied by improvements in ANS function, as reflected by SSR parameters (latency and amplitude) and HRV following BB stimulation. Improvements in autonomic regulation may subsequently enhance cardiovascular recovery, exercise tolerance, handgrip strength, and aerobic fitness biomarkers, thereby contributing to a safer and more confident RTS process.

## 4. Practical Applications

If the intervention proves effective, binaural beats music-based stimulation may represent a non-invasive, low-cost, and easily applicable complementary strategy for sports rehabilitation. Such an intervention could be integrated into warm-up routines, pre-training preparation, or functional rehabilitation sessions in professional athletes with chronic lower-limb musculoskeletal injuries.

From a clinical perspective, this approach may assist physiotherapists, sports medicine physicians, athletic trainers, psychologists, and rehabilitation specialists in addressing psychological and physiological barriers to RTS. Binaural beats may help reduce stress-related arousal, support autonomic regulation, enhance movement confidence, and improve psychological readiness in athletes experiencing fear of reinjury. In addition, adding acoustic stimulation during warm-up and rehabilitation may provide useful information regarding its potential role in supporting attentional control, concentration, decision-making, and sport-specific performance.

The findings of this study may therefore contribute to the development of evidence-based complementary rehabilitation strategies aimed at reducing kinesiophobia, supporting ANS regulation, and facilitating safer reintegration into open skills sports.

## 5. Strengths and Limitations

A major strength of the present study is its double-blind randomized controlled trial design, which minimizes selection and assessment bias and enhances methodological rigor. The inclusion of experimental, placebo, and control groups allows the specific effects of binaural beats to be examined beyond the potential effects of music exposure and verbal guidance alone. In addition, the simultaneous evaluation of psychological outcomes, ANS function, handgrip strength, cardiovascular regulation (HRV), and fitness biomarkers provides a comprehensive biopsychophysiological assessment of professional athletes in open skill sports with chronic MSK-I. The inclusion of follow-up measurements four weeks after completion of the intervention further enables the examination of short-term maintenance effects.

Another strength of the study is the standardization of the intervention protocol. The binaural beats music-based intervention will be administered through headphones to ensure accurate binaural auditory stimulation. Furthermore, intervention duration, listening frequency, warm-up integration, auditory guidance, and environmental instructions will be standardized across participants to reduce variability in auditory exposure and improve intervention fidelity. The use of validated questionnaires and standardized physiological and functional assessment procedures further strengthens the reliability of the outcome measures and the internal validity of this study.

Nevertheless, several limitations should be acknowledged. First, participants will be recruited from collaborating sports clubs within the Attica region, Greece, which may introduce selection bias and limit the generalizability of the findings to athletes from other geographical regions, competitive levels, or sporting disciplines. Second, the study focuses exclusively on chronic lower-limb MSK-I, restricting the applicability of the findings to acute injuries, upper-limb musculoskeletal conditions, or post-surgical populations.

Additional limitations include heterogeneity in injury characteristics, such as injury duration, severity, diagnosis, rehabilitation history, training load, and competitive level, all of which may influence recovery and intervention responsiveness. Although the inclusion of both male and female athletes enhances the generalizability of the study, the sample is not specifically powered to examine sex-specific effects. Therefore, any sex-related differences in psychological, autonomic, or fitness-related responses will be interpreted with caution and considered exploratory. Finally, environmental listening conditions during independently completed intervention sessions may not be fully controlled, potentially introducing variability in participants’ exposure to the auditory intervention.

## 6. Conclusions

This study protocol describes a double-blind randomized controlled trial designed to investigate the effects of a binaural beats music-based intervention on kinesiophobia of reinjury, autonomic nervous system function, and fitness biomarkers in professional athletes with chronic lower-limb musculoskeletal injuries. By integrating psychological, autonomic, functional, and fitness-related outcomes, the study may provide a comprehensive understanding of how auditory stimulation could influence biophysiological functions.

The findings of the present study may contribute to the development of complementary, non-invasive rehabilitation strategies aimed at optimizing both psychological and physiological recovery in injured athletes. Future research should investigate whether the effects of binaural beat–based interventions differ between athletes participating in open-skill and closed-skill sports, particularly regarding kinesiophobia, autonomic nervous system regulation, cognitive performance, and physical fitness outcomes. In addition, further randomized controlled trials are warranted to evaluate the effectiveness of binaural beat interventions following surgical rehabilitation procedures, such as anterior cruciate ligament reconstruction and shoulder reconstruction, with particular emphasis on return-to-sport (RTS) outcomes, fear of reinjury, psychological readiness, and functional recovery. Finally, future studies should incorporate electroencephalography (EEG) alongside autonomic and psychological assessments to further elucidate the neurophysiological mechanisms underlying binaural beat stimulation and its potential role in enhancing rehabilitation outcomes in injured athletes.

## Figures and Tables

**Figure 1 healthcare-14-02129-f001:**
[figure not shown]
CONSORT Flow diagram.

**Figure 2 healthcare-14-02129-f002:**
[figure not shown]
Electrode placement for Sympathetic Skin Response (SSR) recording from the upper limb. Surface electrodes were positioned according to the standard SSR recording protocol. (A) Active recording electrode placed on the palmar surface of the hand, (B) reference electrode positioned on the dorsal aspect of the hand, and (C) ground electrode placed on the distal forearm. This electrode configuration was used for all upper-limb SSR recordings throughout the study [62].

**Figure 3 healthcare-14-02129-f003:**
[figure not shown]
Electrode placement for Sympathetic Skin Response (SSR) recording from the lower limb. Surface electrodes were positioned according to the standardized SSR recording protocol. (A) Active recording electrode placed on the plantar surface of the foot (sole), and (B) reference electrode positioned on the dorsal aspect of the foot. This electrode configuration was used for all lower-limb SSR recordings performed throughout the study to evaluate sudomotor sympathetic function [62].

